Older adults with MCI and dementia are at increased risk for Neuro-Cardiovascular Instability (NCVI) and Orthostatic Hypotension (OH) [28, 29]. NCVI/OH may even influence clinical progression and mortality in those with cognitive impairment and dementia [30, 31]. The VN is the primary mediator of neuro-cardiovascular reflexes including the baroreceptor response that maintains cerebrovascular perfusion during systemic hypotension [35]. Given the prominent role of the VN in NCVI, it is crucial to understand the effect of VN modulation on NVCI phenotypes in older adults with MCI, who may be at greater risk of OH and other NCVI phenotypes. Whilst VN stimulation may exert beneficial effects on NCVI, it is of paramount to establish its safety in older adults with MCI. Key measures to assess the neuro-cardiovascular response to acute tVNS stimulation include: measurement of Heart Rate Variability (HRV) – a marker of VN activity, peripheral (finometry based beat-to-beat blood pressure assessment) and central (assessed via Near Infrared Spectroscopy [NIRS]) responses to active stand.

Vagally-mediated transient reductions cerebral perfusion in those with MCI could be deleterious, as those with MCI have reduced cerebral blood flow compared to Cognitively Unimpaired (CU) individuals at baseline [32]. tVNS, however, specifically exploits the peripheral anatomy of the VN, and it is the right cervical VN that provides most negatively chronotropic effects via the sinoatrial node. Hence only the cymba conchae of the left ear is stimulated during tVNS, as the left VN provides cardiac innervation via the atrioventricular node which is less likely when stimulated to cause bradycardia [33, 34].

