Oxygenation of cerebral tissue can be noninvasively measures using tools such as NIRS devices. NIRS devices project near-infrared light into underlying tissue (such as cerebral cortical tissue) and measures the backscatter of this light using detectors. Based on the amount of backscatter, the concentration of oxygenated haemoglobin and deoxygenated haemoglobin can be determined and from this information the Tissue Saturation Index (TSI; a measure of tissue oxygenation) can be determined [35]. The TSI has emerged as an objective surrogate marker of cerebral perfusion, suitable for clinical testing of dynamic cerebrovascular hemodynamics during standing [36] and has been evaluated as a marker of oxygenation during tVNS and cognitive testing as well [37]. There is a known age-related reduction in resting-state TSI in the prefrontal cortex in older adults [38] and persons with MCI have lower resting state TSI levels compared to healthy controls [39, 40]. Whether frontal TSI could be augmented by tVNS in a population with MCI remains to be explored.

The Vagus Nerve Stimulation in Mild Cognitive Impairment (VINCI-AD) study will examine the use of an easy-to-use, tVNS device in MCI. VINCI-AD will determine the safety (adverse events ascertainment, peripheral and central haemodynamic responses to active stand) and feasibility of tVNS as a potential treatment in older adults with MCI. Pre-specified exploratory secondary analysis will assess the impact of acute tVNS on cognitive function (namely associative memory, spatial memory, inhibitory control, language and working memory) to provide potential effect size estimates to inform future clinical trials of tVNS in MCI.

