## Methods/design

### Study design

VINCI-AD is a single-site, single-blind, sham-controlled crossover pilot study in patients with amnestic MCI. Each participant is assessed at baseline (no stimulation) followed by randomisation to both sham stimulation and active tVNS stimulation over two subsequent study visits. The study comprises a baseline assessment (visit 1) followed 7–10 days later by either an active or sham stimulation study visit and again 7–10 days later by a third visit wherein the final condition (active or sham) will be undertaken. The inclusion of a sham stimulation condition is to confound for potential unblinding, which is common in device trials. Participants will be enrolled and consented by study clinician (HD). Please see Fig. 1 for an illustration of randomisation and sham stimulation technique.

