### Sample size

To establish the safety and feasibility of tVNS in a population of older adults with MCI, VINCI-AD aims to recruit 40 participants for inclusion. This sample size is based on previous literature which investigated the effects of tVNS in healthy young adults [19–21, 23, 55] and also CU older adults [47]. Potential effect sizes from the results of this feasibility study will inform an accurate power calculation for future definitive trials.

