### Statistical analysis

VINCI-AD will assess the safety and feasibility of tVNS in older adults with MCI. All participants will be included in final analysis in an “intention-to-treat” fashion. Statistical analysis will be conducted using MATLAB (The MathWorks, Inc., Natick, MA, USA), SPSS (IBM SPSS Statistics for Windows, Armonk, NY: IBM Corp) and GraphPad Prism (GraphPad Software, Inc., San Diego, CA, USA). We anticipate that TSI analysis will require cleaning to remove “noisy” channels i.e. removing large spikes (changes in oxy-Hb larger than 0.5 mM/mm in amplitude); noisy channels will be excluded from analyses and data analyses will utilise software Platform for Optical Topography Analysis Tools [56] with a bandpass filter with cut-off frequencies of 0.01–0.8 Hz to remove instrumental or physiological noise [57].

In the first instance, descriptive statistics will be described for the cohort, reported as means (with standard deviations) or medians (with inter-quartile ranges) and proportions (percentages) as appropriate.

The primary aim of the current study is to assess the safety and feasibility of tVNS in MCI. To assess safety, a chi-square test will compare the number of adverse events reported during the active vs. sham condition. Further safety assessment will elicit symptoms experienced during active stand (using a chi-square statistic), peripheral (beat-to-beat blood pressure response to orthostasis – using mixed-effects linear regression with study condition as the independent variable, with random intercepts for study participant) and central (TSI – also assessed using a linear mixed-effects model). Feasibility will be reported via recruitment rates, successful enrolment, and study completion in proportions and percentages. Tolerability will be assessed using Likert scales, which will be compared between active and sham conditions using paired between-condition statistics (t-test if normally distributed or non-parametric equivalent). Descriptive statistics will be used to report acceptability using the modified Kettle test.

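### Orthostatic symptoms on active stand get only a chi-square test of no difference; with 40 participants a non-significant result cannot carry the stated aim of establishing safety

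*Protocol article*

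**What the plan says.** The Background of the protocol article states the aim: "VINCI-AD will determine the safety (adverse events ascertainment, peripheral and central haemodynamic responses to active stand". It also says that "it is of paramount to establish its safety in older adults with MCI". The Sample size section repeats it: "To establish the safety and feasibility of tVNS in a population of older adults with MCI, VINCI-AD aims to recruit 40 participants for inclusion". Table 1 lists active stand with TSI under the primary safety outcome, at all three visits. The Abstract says that safety is assessed primarily through adverse events, and the Statistical analysis section treats active stand as a further safety assessment.

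For the active stand, the Statistical analysis section names three analyses:

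- **Symptoms:** "Further safety assessment will elicit symptoms experienced during active stand (using a chi-square statistic".
- **Blood pressure:** "using mixed-effects linear regression with study condition as the independent variable, with random intercepts for study participant".
- **TSI:** a linear mixed-effects model as well.

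The design is within-person: "Each participant is assessed at baseline (no stimulation) followed by randomisation to both sham stimulation and active tVNS stimulation over two subsequent study visits". The number 40 rests on precedent: "This sample size is based on previous literature which investigated the effects of tVNS in healthy young adults", and on a study in cognitively unimpaired older adults. No alpha, power, effect size or symptom rate is given. No confidence interval or other bound is tied to the symptom comparison.

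**The concern.** The null hypothesis of the chi-square is no difference, and the hoped-for safety conclusion is no harmful difference. A favourable reading can therefore come only from failing to reject, and failing to reject becomes more likely as information shrinks, for example when participants miss a visit. The Background itself describes people with MCI as being at raised risk of orthostatic hypotension, and it warns that transient falls in cerebral perfusion could harm them. If the symptom comparison is reported as a bare non-significant p-value, the reader cannot tell whether harm was excluded or the study was too small to see it.

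This is a separate matter from applying an unpaired chi-square to paired data. A correctly paired test of no difference has the same limitation, as the working shows.

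**Working it through.** **The plan's own figure.** N = 40 cannot be reproduced, because the protocol gives no alpha, power, effect size or event rate. The check is therefore of what 40 participants can show.

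**Inputs from the protocol.** 40 participants, each observed under active and sham; chi-square for symptoms.

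**Assumptions (not in the protocol).** Active against sham as the two conditions compared; two-sided alpha 0.05; no drop-out; sham symptom rate from 5% to 30%, doubled under active; latent within-person correlation 0.3 to 0.7.

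**Step 1: formula check, treating conditions as independent.** With q = 1 − p, and p̄ and q̄ the averages over the two conditions,

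power ≈ Φ{[(p₂ − p₁)√n − 1.96√(2p̄q̄)] / √(p₁q₁ + p₂q₂)}.

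- 10% to 20%: (0.1 × 6.325 − 1.96 × 0.505) / 0.5 = −0.715. Power is 24%, so the miss rate is 76%.
- 20% to 40%: (0.2 × 6.325 − 1.96 × 0.648) / 0.632 = −0.008. Power is 50%, so the miss rate is 50%.

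**Step 2: simulation with pairing.** 40 correlated binary pairs per trial were generated from bivariate normal thresholds, with 40,000 trials per scenario. Each was tested with the Pearson chi-square without continuity correction and, for comparison, the exact McNemar test. The ranges run over correlations 0.3, 0.5 and 0.7.

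| Sham to active | Chi-square miss rate | Exact McNemar miss rate |
|---|---|---|
| 5% to 10% | 87–91% | 96–97% |
| 10% to 20% | 77–81% | 81–84% |
| 20% to 40% | 50% | 37–53% |
| 25% to 50% | 31–34% | 19–36% |
| 30% to 60% | 14–18% | 8–21% |

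The chi-square column is the one that applies to the plan as written. The McNemar column shows that correcting for pairing does not remove the problem at low symptom rates.

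**Step 3: what a non-significant result can hide.** Suppose 6 participants have symptoms only on active and 2 only on sham.

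- Exact McNemar, 6 of 8 against one half: p = 0.29.
- Chi-square if nobody is symptomatic on both (6/40 against 2/40): 0.1² / (0.1 × 0.9 × 2/40) = 2.22, p = 0.14. With 4 participants symptomatic on both, p = 0.26.
- Risk difference: (6 − 2)/40 = 10 points. Standard error: √(8 − 4²/40)/40 = √7.6/40 = 0.0689. Wald 95% CI: 0.10 ± 1.96 × 0.0689, which is −3.5 to +23.5 points.

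Either test is non-significant, yet the data are compatible with about 23 extra symptomatic participants per 100.

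**The case against.** The strongest reply has four parts.

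- **No decision rule is stated.** A reader might infer that the study will call tVNS safe if p > 0.05. The protocol does not say so: it says safety will be assessed and reported. This stands. The point is that such a reading is left open, because no other basis is named for the symptom statement.
- **Two of the three measures are not bare tests.** A reader might infer that blood pressure and TSI are also handled only by significance tests. The planned mixed models give a condition difference and a standard error, from which an interval follows directly. This stands, and the concern is confined to symptoms; for the other two only a reporting line is asked for.
- **It is a pilot, and the article is condensed.** Confidence intervals and margins often sit in a fuller document, and a pilot need not be sized for non-inferiority. This stands against demanding a margin. It does not dispose of the point, because the article does specify the symptom inference and chose one that cannot support its stated aim.
- **The miss rates depend on assumed event rates.** This also stands. From a 30% sham rate the chi-square detects a doubling more than 80% of the time, so it would be wrong to say that the test fails at every plausible rate.

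Active stand is also secondary to adverse events in the Abstract, although Table 1 puts it under the primary safety outcome.

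**Conclusion.** The concern holds in a limited form. For orthostatic symptoms, the protocol pairs an aim of establishing safety with a test that can only detect a difference, in a sample chosen by precedent. Under the assumptions listed, the named chi-square misses a doubling about half the time from a 20% sham rate and about 77–91% of the time from 10% or 5%. From 25% and 30% it misses about 31–34% and 14–18%. The true symptom rate is unknown, so the whole range should be quoted with its assumptions. The documents do not support the stronger claims that a null result will be declared safe, that the blood pressure and TSI analyses share the defect, or that a pre-set tolerable worsening is required; they give no basis for choosing one.

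**What to change.** In the Statistical analysis section:

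1. Replace the chi-square as the basis of the active-stand symptom statement with the paired difference in the proportion of participants with any orthostatic symptom, active minus sham, with a 95% CI for paired proportions. A score-type interval is preferable to the Wald interval used above for illustration when discordant pairs are few.
2. Report active minus no stimulation in the same way. Visit 1 always comes first, so this contrast is not randomised and should be read with that caveat.
3. Report the blood pressure and TSI condition contrasts from the planned mixed models with their 95% CIs.
4. State that p > 0.05 alone will not be reported as evidence of safety, and that the confidence limit on the harmful side will be given alongside the conclusion.

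The cost is a few sentences, with no extra participants or procedures. The downside is that the symptom result may have to be described as inconclusive. No non-inferiority margin needs to be set.

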### Safety and tolerability of tVNS in MCI

The risk associated with use of the NEMOS © Cerbomed tVNS device is minimal as published data of the safety profile shows minimal adverse events. The most common adverse events reported include local skin tingling, burning, redness, itching, tinnitus or headache which occur in up to 18% of participants, and tends to resolve quickly after discontinuation of the use of the device [42]. Due to the theoretical risk of increasing cardiac vagal-mediated bradycardias or hypotensive episodes by stimulating the right VN, participants will have stimulation of the left ear only.

During the active and sham stimulation conditions, safety will be recorded by completion of the following:

Contemporaneous recording of any adverse events reported by participants whilst undergoing either active or sham stimulation.Likert-Based Questionnaires (See Additional File 2) will assess for established side effects previously reported with tVNS: pain, skin discomfort, tingling, headache and tinnitus. These will be administered both during active and sham stimulation.Detailed assessment of subjective (OH symptoms including faintness, light-headedness), peripheral (beat-to-beat blood pressure) and central (TSI) haemodynamic responses to active stand.
Briefly, participants will undergo active stand from supine to standing. After lying supine for 5 min, participants will be asked to stand as fast as they can. Beat-to-beat blood pressure and heart rate responses (assessed via the Finapres© NOVA) will be monitored during active stand and for three minutes after. To standardise assessments, all assessments are all taken at the same time each day, and all routine medications are taken as usual each morning. OH is defined by consensus as a sustained reduction of systolic blood pressure (SBP) of at least 20 mmHg or diastolic blood pressure (DBP) of 10 mmHg within 3 min of standing [43].
During active stand, cerebral oxygenation (TSI) will be estimated using NIRS-based analysis software. TSI analysis will be undertaken using the PortaLite OxySoft© NIRS device (PortaLite, Artinis Medical Systems B.V., Elst, The Netherlands) and the light emitting diode will be placed on clean skin on the right forehead, devoid of moisture or oil, and secured with a black headband. TSI readings are transferred via Bluetooth in real-time and will give an approximation of tissue oxygenation during rest, active stand, and all cognitive assessments.

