Following assessment, participants will be given contact details of the principal investigator and study coordinator at the hospital who they can contact if they have concerns, or any new symptoms arise. Any adverse events will be diarised during the intervention and closely monitored until resolution. Data of participants who discontinue or deviate from the study protocol will be retained for intention to treat analysis.

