### Randomisation

Patients who provide informed consent to participate and who fulfil eligibility criteria will be enrolled into the study. Initial visit (visit 1) involves baseline assessments of neurocardiovascular, cognitive, and inflammatory status. Participants are then randomised to either active or sham stimulation condition at the following visit and then to the alternate condition at the final visit. Participants are blinded to the active or sham stimulation condition but study researchers are not (i.e. single-blinded). Please see Fig. 1 for randomisation strategy.

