Exploratory secondary aims of this study (cognitive testing, HRV analysis, inflammatory responses) will be analysed using a repeated three – way analysis of variance (ANOVA) if parametric or Kruskal-Wallis test if non-parametric analysis required, with Bonferroni corrections for multiple comparisons. We will explore the effects of concentrations of pro-inflammatory plasma cytokines on cognitive and neurocardiovascular characteristics. Missing data will be handled by applicable statistical methods including multiple imputation.

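### The paired tolerability test uses only complete active–sham pairs unless scores are imputed, which does not fit the plan to include all participants and retain discontinuers' data

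*Protocol article*

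**What the plan says.** - **Test.** Under Statistical analysis, the tolerability Likert scores are to be "compared between active and sham conditions using paired between-condition statistics (t-test if normally distributed or non-parametric equivalent".
- **Outcome status.** Table 1 lists acceptability and tolerability as a primary outcome, measured with Likert questionnaires at Visits 2 and 3.
- **Timing of scores.** Safety and tolerability of tVNS in MCI says of the questionnaires: "These will be administered both during active and sham stimulation".
- **Order of conditions.** Randomisation: "Participants are then randomised to either active or sham stimulation condition at the following visit and then to the alternate condition at the final visit". Under Study design, the two stimulation visits are 7–10 days apart.
- **Analysis population.** Statistical analysis says "All participants will be included in final analysis in an" intention-to-treat fashion. Safety and tolerability adds: "Data of participants who discontinue or deviate from the study protocol will be retained for intention to treat analysis".
- **Missing data.** The paragraph on the exploratory aims ends: "Missing data will be handled by applicable statistical methods including multiple imputation". No sentence says how a missing active or sham Likert score enters the paired test.
- **Neighbouring outcomes.** The same paragraph as the tolerability test assigns linear mixed models to the blood pressure and TSI responses to standing.
- **Completion.** "Feasibility will be reported via recruitment rates, successful enrolment, and study completion in proportions and percentages".

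**The concern.** A paired t-test, or its usual non-parametric equivalent (the Wilcoxon signed-rank test), works on within-person differences. A participant with one score has no difference and contributes nothing unless the other score is imputed.

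In this crossover the first score exists before the second visit. A participant who receives active stimulation at Visit 2, tolerates it badly and does not come back has a recorded poor active score that the test sets aside. A participant with the same reaction at Visit 3 already has a sham score and stays in. Inclusion can therefore depend on the randomised order and on the outcome being measured.

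At stake is the active-versus-sham estimate for an outcome listed as primary. If people leave because of active stimulation more often than because of sham, the remaining pairs understate how much worse active was tolerated.

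**Working it through.** **No figure in the plan to reproduce.** Sample size says "VINCI-AD aims to recruit 40 participants for inclusion", on the basis of earlier literature. It gives no power, effect size, SD, correlation or drop-out rate. What follows is an illustration; apart from the 40, every input is an assumption.

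**Inputs.** N = 40 (Sample size). Assumed: 20 participants active-first (the article states no allocation ratio); discomfort scores normal with SD 1; true active-minus-sham difference 0.50; within-person correlation r of 0.3, 0.5 or 0.7; the k worst-scoring active-first participants leave before Visit 3; nobody else leaves.

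**Pairs left.** 40 − k: 39, 38, 36 and 34 for k = 1, 2, 4 and 6 (5%, 10%, 20% and 30% of the 20).

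**Formula.** A participant whose active score lies z SDs above its mean has an expected active-minus-sham difference (1 − r)·z above the average. Removing the k highest of 20 active scores therefore lowers the mean of the remaining pairs by

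shift = (1 − r) × S_k / (40 − k),

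where S_k is the expected sum of the k largest of 20 standard normal values: S_1 = 1.867 and S_6 = 6.663.

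- k = 1, r = 0.5: 0.5 × 1.867 / 39 = 0.024, so the estimate is 0.50 − 0.024 = 0.476.
- k = 6, r = 0.3: 0.7 × 6.663 / 34 = 0.137, so the estimate is 0.50 − 0.137 = 0.363.

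**Simulation** (20,000 runs per setting), mean complete-pairs estimate and understatement of 0.50:

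| k | r = 0.3 | r = 0.5 | r = 0.7 |
|---|---|---|---|
| 1 | 0.467 (7%) | 0.476 (5%) | 0.485 (3%) |
| 2 | 0.440 (12%) | 0.459 (8%) | 0.475 (5%) |
| 4 | 0.395 (21%) | 0.425 (15%) | 0.454 (9%) |
| 6 | 0.362 (28%) | 0.404 (19%) | 0.441 (12%) |

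The formula and the simulation agree. At r = 0.5, the power of the paired t-test (two-sided 5%) falls from about 0.87 with full data to 0.83, 0.80, 0.71 and 0.64 for k = 1, 2, 4 and 6.

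**Keeping the single scores.** In the same setting, imputing the missing sham score by regression on the active score gave 0.495 to 0.505 throughout (2,000 runs per setting). A mixed model with condition, period and a random participant effect, fitted to all recorded scores, gave 0.48 to 0.52 (150 runs per setting; k = 2, 4, 6). Either route removes most or all of the shift under these assumptions.

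**Direction.** If sham-first participants leave after a bad sham session, the same formula applies with the opposite sign. With equal numbers and equal selection in both sequences, the two shifts cancel.

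**The case against.** **No completers-only rule is stated.** A reader might infer that the plan restricts the tolerability test to participants with both scores, or that it flatly contradicts its intention-to-treat statement. The article says neither. The missing-data sentence is unqualified, and it closes the whole Statistical analysis section as well as the exploratory paragraph. A paired comparison with imputed scores would be compatible with every statement. This stands: the exclusion is the default result of the named test, not a written rule.

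**Detail left to a fuller document.** How imputation enters one test is commonly settled in an analysis plan, and that gap alone would be no finding. What remains is that the article names a specific test which, on recorded data, does not deliver the population it promises.

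**Size.** A reader might infer that the effect could be halved. That needs a constructed case. Suppose 4 of 40 score 8 on active while every other score is 1, and the 2 intolerant active-first participants leave: the true difference is 4 × 7/40 = 0.70 and the paired estimate is 2 × 7/38 = 0.37. Those scores and that drop-out are invented. The article's figure of up to 18% cannot supply them: it is an occurrence rate for common side effects that tend to resolve quickly, not a rate of intolerance or withdrawal.

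**Direction.** A reader might infer that active must look better tolerated than it was. Sham also delivers current, at the earlobe, and drop-out after a bad sham session biases the other way. The direction is therefore conditional.

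**Drop-out is visible elsewhere.** Adverse events are recorded in both conditions and compared, and completion is reported. This is true and limits the harm, but neither corrects the active-versus-sham Likert estimate.

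**Conclusion.** The point holds as a mismatch between the named test and the stated analysis population. Unless scores are imputed, the paired test omits recorded Likert scores from participants who stop after Visit 2, and the article does not tie its imputation sentence to those scores. The estimate favours active tVNS only if drop-out follows intolerance of active more than of sham.

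The size cannot be derived from the article. Under the smooth-score assumptions above it is small with little drop-out (about 3–7% understatement with one worst-scoring active-first quitter) and moderate with much (12–28% with six). It could be larger if intolerance is concentrated in a few people who all leave, but the article gives no basis for expecting that. This is an inexpensive improvement to the analysis of a primary outcome, not evidence that the tolerability result will be wrong.

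**What to change.** In Statistical analysis, replace the paired test with a mixed model for each Likert item: condition and period as fixed effects, participant as a random effect, and every recorded score included. Use an ordinal mixed model where an item is strongly skewed. The article already uses linear mixed models for blood pressure and TSI, so the approach is not new to the plan, and it also adjusts for period.

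Alongside it, tabulate by condition the number of participants who stopped the session or did not return for a device-related reason. The model relies on the recorded score explaining the drop-out, and the table shows what the model cannot.

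A narrower alternative is to keep the paired test and state that multiple imputation covers the Likert scores. That would reconcile the statements, but without the period adjustment.

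Cost: a wording change and slightly more modelling. No additional Likert scores are needed, though the reason for stopping or not returning must be recorded. With 40 participants, items on which almost everyone gives the lowest score may not support a stable model and may need a simpler summary.

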**Fig. 1 Fig1:**
[figure not shown]
Method of crossover

Our study will follow the Standard Protocol Items: recommendations for Interventional Trials (SPIRIT) guidelines [41]. Table 1 illustrates the SPIRIT flow diagram summarising study procedures, outcome measures, randomisation and assessments for each study visit.

**Table 1 Tab1:** Flowchart of VINCI-AD Protocol Timeline

			Study Period					
			Screening (day − 90 to day − 7)	Visit 1 (day 0)		Visit 2 (day 7–10)		Visit 3 (day 14–17)
Enrolment								
- Eligibility Screen			x					
- Informed Consent			x					
Intervention								
- Baseline assessments (no stimulation)				x				
- Active (left cymba conchae) stimulation						ø		ø
- Sham (left earlobe) stimulation						†		†
Assessments								
- General assessment, vitals, medication changes				x		x		x
- Primary Outcome: Safety								
- Assess for AE/ SAEs						x		x
- Active stand with TSI				x		x		x
- Primary Outcome: Acceptability and Tolerability								
- Likert scale questionnaires						x		x
- Cognitive assessments								
- FNAT				x		x		x
- SART				x		x		x
- SHQ				x		x		x
- Verbal word learning				x		x		x
- Semantic fluency				x		x		x
- Digit span forwards				x		x		x
- Digit span backwards				x		x		x
- Verbal word recall				x		x		x
- Verbal word recognition				x		x		x
- Frontal Oxygenation								
- Cognitive testing TSI				x		x		x
- Neurocardiovascular assessments								
- HRV				x		x		x
- Serum / Plasma venepuncture								
- Inflammatory cytokine panel				x		x		x
- Device usability assessment								
- Kettle test								x

Ø = active stimulation randomisation: participant randomised to either sham or active stimulation at Visit 2 and alternative stimulation site at Visit 3

† = sham stimulation randomisation: participant randomised to either sham or active stimulation at Visit 2 and alternative stimulation site at Visit 3

AE – Adverse event; SAE – Serious adverse event; FNAT – Face Name Association Task; SART – Sustained Attention Response Task; SHQ – Sea Hero Quest Tas; NIRS – functional Near Infrared Spectroscopy; HRV – Heart Rate Variability; TSI – Tissue Saturation Index

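### The paired test for the Likert tolerability scores leaves out the randomised order, so any change between the two stimulation sessions is counted as error; adding visit is a near-free improvement

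*Protocol article*

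**What the plan says.** Under Study design, the protocol article describes a two-period crossover that follows an unstimulated first visit: "Each participant is assessed at baseline (no stimulation) followed by randomisation to both sham stimulation and active tVNS stimulation over two subsequent study visits". The second stimulation session follows the first "again 7–10 days later by a third visit wherein the final condition (active or sham) will be undertaken". The Randomisation section confirms that order is the randomised factor: "Participants are then randomised to either active or sham stimulation condition at the following visit and then to the alternate condition at the final visit". For the allocation strategy it refers to Fig. 1, which is not shown.

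Table 1 has a row headed "Primary Outcome: Acceptability and Tolerability", with Likert questionnaires at Visits 2 and 3. The section on safety and tolerability lists the items: pain, skin discomfort, tingling, headache and tinnitus.

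For these scores, Statistical analysis names the test: they are "compared between active and sham conditions using paired between-condition statistics (t-test if normally distributed or non-parametric equivalent". No analysis in the article includes visit, period or order. The blood pressure model is described as "using mixed-effects linear regression with study condition as the independent variable, with random intercepts for study participant".

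**The concern.** A paired test pools every participant's active-minus-sham difference. It accounts for the pairing but not for which condition came first. The scores are subjective ratings of a stimulation worn in only two sessions, with a participant-selected amplitude, so ratings could drift from the first session to the second through novelty or familiarity. Such a drift enters the difference with opposite sign in the two orders, and the paired test cannot tell it from noise.

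At stake is the precision of the active-sham comparison on an outcome labelled primary. If the two orders are unequal among the analysed pairs, the estimate itself is also affected. This is a question about a stated method, not about a detail left out of a condensed article.

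**Working it through.** **Inputs from the protocol article.** Planned number: "VINCI-AD aims to recruit 40 participants for inclusion". Design: two orders over Visits 2 and 3. Test: paired t-test or its non-parametric equivalent. The figure of 40 cannot be reproduced from a power calculation, because none is given: "This sample size is based on previous literature which investigated the effects of tVNS in healthy young adults", and the same sentence also cites work in cognitively unimpaired older adults.

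**Assumed inputs.** Two-sided 5% level; 40 complete pairs; normal differences with SD 1 within each order; session change π from 0 to 1 SD; orders 20/20, with 24/16 and 25/15 as unequal cases. The true effect τ is set at 0.454 SD, which gives 80% power at N = 40 with no session change (noncentral t, 39 df).

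**Model.** Let D = active − sham for one participant, and π = the change in rating from the first to the second stimulation session.
- Active first: mean of D = τ − π.
- Sham first: mean of D = τ + π.

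**Error term.** With p the share given active first, pooling the orders adds 4p(1−p)π² to the variance of D. The expected sample variance is 1 + 4p(1−p)π² × N/(N−1). At 20/20, 4p(1−p) = 1:
- π = 0.3: 1 + 0.09 × 40/39 = 1.09
- π = 0.5: 1 + 0.25 × 40/39 = 1.26
- π = 1.0: 1 + 1.00 × 40/39 = 2.03

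The standard error therefore grows by √1.09 = 1.04, √1.26 = 1.12 and √2.03 = 1.42.

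**Estimate.** The mean of D is shifted by π × (n sham first − n active first)/N. At 20/20 this is zero. At 24 active first and 16 sham first, π = 0.5 gives 0.5 × (16 − 24)/40 = −0.10 SD. At 25/15 it gives 0.5 × (15 − 25)/40 = −0.125 SD. The sign reverses if the larger group has sham first.

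**Comparator.** The period-adjusted estimate is the average of the two order-specific means of D, with pooled within-order variance and 38 df. π cancels: [(τ − π) + (τ + π)]/2 = τ.

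**Simulated results** (at least 20,000 trials per setting), orders 20/20:

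| Session change (SD) | Paired power | Paired false-positive rate | Adjusted power |
|---|---|---|---|
| 0 | 80% | 5% | 80% |
| 0.25 | 78% | 4.1% | 80% |
| 0.3 | 77% | 4.2% | 80% |
| 0.5 | 73% | 2.8% | 80% |
| 1.0 | 50% | 0.5% | 80% |

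The rates at 0.25 and 0.3 come from separate runs and differ only by simulation error. The adjusted false-positive rate is about 5% throughout.

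**Unequal orders, given that split, with π = 0.5.**
- 24/16: paired power is 50% if the larger group has active first and 89% if it has sham first; the false-positive rate is about 6%.
- 25/15: paired power is 44% or 92%, with a false-positive rate of about 8%.
- The adjusted analysis gives about 78% (24/16) and 77% (25/15) power, and about 5% false positives.

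**Averaged over allocation.** If each participant were allocated by an independent 1:1 draw, the paired test's false-positive rate is 5.0–5.1% for π = 0.25, 0.5 and 1.0. Under that scheme, 24/16 or worse has probability 0.27, 25/15 or worse 0.15, and exactly 20/20 0.13. Whether that scheme applies is not known.

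**Cost when π = 0.** At 20/20 the adjusted standard error is ½√(1/20 + 1/20) = 0.158, the same as 1/√40. At 25/15 it is ½√(1/25 + 1/15) = 0.163, and power is 77% instead of 80%.

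**The case against.** The paired test is a recognised simple analysis for a small randomised-order pilot, and randomising the order protects its validity. A reader might infer from the unequal-order figures that the planned test is biased or has an inflated false-positive rate. The document does not support that. Those figures hold only given a particular realised split. Averaged over simple randomisation the test keeps its 5% level, and with balanced orders it is unbiased and conservative. The allocation scheme is in a figure that is not shown, so imbalance may be prevented by design, although missed third visits could still unbalance the analysed pairs.

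The session change is an assumption too. Nothing in the article gives its size, and at 0.25 SD or less with 20/20 orders the loss is about 2 points of power, similar to the price of adjusting at 25/15 when there is no change. If most Likert ratings sit at the floor, the non-parametric branch would apply; the figures here are for the t-test only.

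A reader might also infer that a non-significant result would be taken to show that active is tolerated as well as sham. No section sets such a rule, and the pilot has no power target. Nor is Visit 2 necessarily the first exposure to the device: the feasibility section has it introduced on three occasions and worn for two sessions. Visit 2 is the first stimulation session.

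These limits reduce the size of the point but do not remove it. The article names a test that omits the factor it randomises. The blood pressure model, as described, also has no visit term, so the observation is not peculiar to the Likert scores. An analysis plan not shown could add the term.

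**Conclusion.** The point holds as one of efficiency, with a conditional effect on the estimate. With balanced orders the paired test is valid and unbiased, but it counts any session change as error. Under the assumed 40 pairs and 0.454 SD effect, power drops from 80% to about 77%, 73% or 50% for changes of 0.3, 0.5 or 1.0 SD. Below about 0.3 SD little is lost. With unequal orders the estimate also shifts by the session change times the imbalance fraction, for example 0.10 SD at 24/16 with a 0.5 SD change. The chance of such a split cannot be judged from what is shown. The conclusion does not extend to a flawed error rate for the planned procedure or to a mistaken claim of equal tolerability. It is a near-free improvement to a stated analysis.

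**What to change.** In Statistical analysis, replace the paired test for the Likert tolerability scores with a two-period crossover analysis:
- If approximately normal: a linear mixed model with condition and visit (2 or 3) as fixed effects and participant as random. With complete pairs this equals half the difference between the two orders in mean Visit 2 minus Visit 3 score.
- If not normal: a rank-sum test of the Visit 2 minus Visit 3 differences between the two randomised orders.

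Report the active-sham difference with its 95% confidence interval from that analysis.

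The change is to wording only and needs no new data or participants. It costs one degree of freedom, with no visible loss of power at 20/20, and about 2–3 points of power at 25/15 if there is no session change.
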